## Abstract

**Background:**

Results of previous studies attest to the greater illness burden of common mental disorders (anxiety and depression) in older Latinos and the need for developing preventive interventions that are effective, acceptable, and scalable. Happy Older Latinos are Active (HOLA) is a newly developed intervention that uses a community health worker (CHW) to lead a health promotion program in order to prevent common mental disorders among at-risk older Latinos. This pilot study tests the feasibility and acceptability of delivering HOLA to older, at-risk Latinos.

**Methods/Design:**

HOLA is a multi-component, health promotion intervention funded by the National Institute of Mental Health (NIMH). This prevention approach will be tested against a *fotonovela*, an enhanced psychoeducation control condition, in a sample of Latino elderly with minor or subthreshold depression or anxiety. A total of 60 older Latinos (aged 60+) will be randomized to receive HOLA or the *fotonovela*. The primary outcomes of interest are recruitment, adherence, retention, and acceptability. Data will also be collected on: preemption of incident and recurrent major depression, generalized anxiety, and social phobia; reduction in depression and anxiety symptom severity; physical functioning; sedentary behaviors; social engagement; and self-efficacy.

**Discussion:**

The results of this study could have implications for other high-risk, highly disadvantaged populations. The development of a health promotion intervention designed to prevent common mental disorders could be a means of addressing multiple disparities (for example, mental health outcomes, mental health service use, stigma) among racial/ethnic minority elderly.

**ClinicalTrials.gov Identifier:**

NCT02371954. Date of registration: 21 January 2015.

## Background

Latinos are the largest and fastest growing segment of the older adult population [1]. High prevalence of common mental disorders (depression and anxiety) combined with mental health service use disparities make older Latinos a high-risk population for whom scalable preventive interventions could have great public health impact [2, 3]. In addition, older Latinos are more sedentary and are disproportionately affected by diabetes and obesity compared to their non-Latino peers [4, 5]. Cultural beliefs about the causes of mental illness and stigma associated with help seeking may further contribute to Latinos’ limited access and low utilization of mental health care [6–8]. These factors underscore the need to create culturally appropriate preventive interventions for older Latinos. Effective approaches to this challenge are likely to involve using non-traditional means (for example, community health workers, health promotion) that are acceptable and scalable.

The Institute of Medicine [9] states that prevention interventions are those that are conducted before subjects meet the formal criteria for a mental disorder. There are three types of prevention interventions: (a) universal prevention is aimed at the general population, regardless of level of risk; (b) selective prevention is aimed at high-risk groups who have not yet developed a mental disorder (such as experiencing a stressful life event, including a change in health status that may limit independence, divorce, losing a family member through death, caring for an ill family member, or unemployment); and (c) indicated prevention is aimed at individuals who have some symptoms of a mental disorder but do not meet diagnostic criteria. Focusing on those at highest risk, particularly the elderly who have subthreshold symptoms (“indicated” prevention), is the most efficient way to address mental illness prevention in later life [10].

Minor and subthreshold depression and anxiety are highly prevalent in older adults and interfere with functioning similar to disorders meeting full Diagnostic and Statistical Manual (DSM) criteria [11–18]. Despite its label, minor (or subthreshold) depression carries a significant public health burden. Minor depression is a debilitating disorder that is associated with psychological suffering and significant decrements in health [15]. It is also a strong risk factor for major depression, and might increase the risk of death in older individuals [11, 12, 15]. Similarly, subthreshold anxiety is associated with significant impairment in social, family, and occupational functioning, poor perceived emotional and physical health and well-being, low satisfaction with daily life, and an increased risk for developing an anxiety disorder [13, 14, 16–18].

Although prevalence rates are high and negative health consequences are numerous and incapacitating, treatment options for minor depression and subthreshold anxiety are limited. Available treatments are difficult to access and only partially satisfactory in reducing symptom burden, sustaining remission, and averting years lived with disability [19–21]. While antidepressant medications are the most widely used modality for treating prevalent cases of major depression and anxiety, their use in subthreshold depression and anxiety is not supported by evidence of effectiveness and is more likely to be associated with adverse effects in older adults [22]. Additionally, older Latinos are less likely to find antidepressant medication acceptable than non-Latino Whites [23]. Thus, psychosocial strategies are more suitable preventive interventions.

Health promotion interventions are behaviorally activating, reduce vulnerability factors, and may be more desirable for reasons of safety and patient preference. Studies have consistently shown that increased physical activity effectively reduces symptoms of depression and anxiety as well as physical functioning risk factors in older adults [24–27]. Similarly, increasing pleasant events has been shown to be an effective intervention for geriatric depression [28]. Social engagement and self-efficacy have also been shown to be important protective factors in preventing late life depression and anxiety [29, 30]. Thus, there may be a synergy between increased physical activity and pleasant events. In this context, a health promotion intervention such as Happy Older Latinos are Active (HOLA) may be particularly promising since it combines these two strategies to reduce vulnerability factors and enhance protective factors associated with late life depression and anxiety. This makes physical activity interventions appropriate for older Latinos, who often have a combination of physical and mental health problems, by minimizing the stigma sometimes associated with antidepressant medication and talk therapy [4, 5, 8].

The number of geriatric mental health specialists is inadequate to meet the current and future needs of the Latino elderly [31–33]. One promising approach is the use of lay community health workers (CHWs) to deliver simple, scalable interventions. CHWs are lay community members who work almost exclusively in community settings and effectively connect consumers to providers in order to promote health and prevent diseases among groups that have traditionally lacked access to adequate care [34]. They have long been accepted as important conduits of health information, particularly in Latin America and as part of health-promotion efforts with diverse populations. CHWs are assumed to be effective because they are part of the communities in which they work — ethnically, socioeconomically, and experientially. They possess an intimate understanding of community social networks, strengths, and health needs; communicate in a similar language; and recognize and incorporate culture to promote health and health outcomes [35, 36]. The use of CHWs has emerged as a strategy to reduce or eliminate health disparities and is an important means of task shifting to enable more efficient utilization of scarce mental health resources [36, 37].

The combination of high exposure to risk factors (comorbid physical and mental health conditions) and disparities in access and engagement in mental health services attests to the greater illness burden of common mental disorders experienced by older Latinos. There is a compelling need for interventions that promote prevention of common mental disorders among Latino elders and are specifically designed to address their views concerning the causes of mental illness, mental health treatment, and stigma towards traditional mental health services.

The three specific aims of this pilot study are:To develop and refine Happy Older Latinos are Active (HOLA), a health promotion intervention, led by a CHW, to address prevention of common mental disorders in a group of older Latinos with minor and subthreshold depression and anxiety.To evaluate the feasibility and potential effectiveness of the newly refined HOLA compared to an enhanced psychoeducation condition with respect to: (a) depression and anxiety prevention and (b) depression and anxiety severity.To evaluate the feasibility and potential effectiveness of HOLA compared to enhanced psychoeducation with respect to: (a) physical functioning; (b) psychosocial functioning (social engagement and self-efficacy); and (c) sleep to manage anxiety/depression.

## Methods

All study methods and protocols were approved by the Internal Review Board (IRB) of the University of Miami (UM; IRB ID: 20140607).

### Participants

The pilot study will randomly assign 60 older (60+) Latino participants with minor or subthreshold depression or anxiety to the HOLA intervention (n = 30) or enhanced psychoeducation (n = 30). The sample size is sufficient to provide meaningful data on the feasibility and the other outcome measures of interest. Additionally, this sample size is consistent with other pilot studies of physical activity interventions [38, 39]. Informed consent will be obtained from each participant. For a detailed description of the inclusion/exclusion criteria, see Table 1.

**Table 1 Tab1:** Inclusion/exclusion criteria

Inclusion criteria	Exclusion criteria
• Self-identify as Latino; • Age 60+; • Have minor depression as defined by a primary DSM-IV Axis I diagnosis of minor depressive disorder or subthreshold depression defined as a score ≥ 3 on the Patient Health Questionnaire (PHQ-2), OR subthreshold anxiety as defined as a score ≥ 3 on the Generalized Anxiety Disorder-2 scale (GAD-2); • Absent of episodes of major depression and anxiety disorders for past 12 months; • Volunteer informed consent; • Have medical clearance for participation in an exercise program by a physician, physician’s assistant, or nurse practitioner; • Agree not to use antidepressant medication (since these subjects could have a partially treated episode of major depression or anxiety and thus would be inappropriate for a prevention trial); • Expect to stay in Miami for the next 12 months	• Currently residing in a nursing or group home; • Have a terminal physical illness expected to result in their death within one year; • Have a diagnosis of dementia, comorbid diagnosis of dementia, or significant cognitive impairment; • Presence of any Axis I psychiatric disorder or substance abuse during preceding 12 months; • History of psychiatric disorders other than non-psychotic unipolar major depression or anxiety disorder; • High suicide risk; intent or plan to attempt suicide in the near future; • Taking cognitive enhancing medication or psychotropic medications (e.g., antidepressants); • Unable to complete 10-meter walk test in less than 23 seconds average; • Heart rate exceeds 170 beats per minute OR systolic blood pressure exceeds 180 during 10-meter walk test; • Chest or leg pain, dyspnea, dizziness, feeling faint, or other significant symptoms while completing 10-meter walk test; • Have contraindications to exercise outlined in the American College of Sports Medicine standards.

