#### Screening

A two-step screening process will be used to identify potential participants (Fig. 2). The first step includes the PHQ-2 [46] to screen for depression, and the GAD-2 [47] scale to screen for anxiety. The Mini Mental Status Exam (MMSE) [48] will be used to screen for dementia. Potential participants must confirm safe participation by not having an acute or severe medical illness. A letter will be sent to the subject’s primary care physician describing the study and inquiring about any conditions prohibiting participation. The second step includes screening for psychiatric diagnosis with the Mini International Neuropsychiatric Inventory (MINI) [49]. The 10-meter walk test will be used to evaluate walking ability. It has demonstrated excellent reliability when used in older adults and shows comparable results as other, longer measures [50].

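### Table 1 admits people by an Axis I diagnosis of minor depressive disorder but excludes any Axis I disorder in the past 12 months without an exception

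*Protocol article*

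**What the plan says.** The Participants section says that the pilot will randomise 60 older "Latino participants with minor or subthreshold depression or anxiety". The aims at the end of the Background describe the same group. For the detailed eligibility criteria, the section refers the reader to Table 1.

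The inclusion column of Table 1 gives three routes of entry:

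- The first reads "Have minor depression as defined by a primary DSM-IV Axis I diagnosis of minor depressive disorder".
- The second is subthreshold depression, defined as a PHQ-2 score of 3 or more.
- The third is subthreshold anxiety, defined as a GAD-2 score of 3 or more.

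A separate inclusion criterion reads "Absent of episodes of major depression and anxiety disorders for past 12 months".

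The exclusion column has two criteria that bear on the first route:

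- The one that covers the past year reads "Presence of any Axis I psychiatric disorder or substance abuse during preceding 12 months". It names no exception.
- The one that covers earlier illness does name exceptions, and its wording is "History of psychiatric disorders other than non-psychotic unipolar major depression or anxiety disorder".

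The Screening section describes two steps. The PHQ-2 and GAD-2 come first, and the MINI follows for psychiatric diagnosis. It states no exemption for minor depressive disorder.

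**The concern.** The protocol itself labels minor depressive disorder an Axis I diagnosis, so a current case falls within an exclusion of any Axis I disorder in the past 12 months. A participant admitted by the first route would be removed by the exclusion column of the same table.

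Two things are at stake. The first is the population: a strictly screened sample would contain no one with diagnosed minor depression, although the aims name that group. The second is a feasibility result. Under the feasibility objective, successful recruitment requires that no more than 20 % of eligible subjects refuse randomisation. Who counts as eligible sets the denominator, and two screeners reading the table differently would classify the same person differently.

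**Working it through.** The check is one of logic, because the plan gives no figure to reproduce. The inputs are the three inclusion routes, the 12-month inclusion criterion and the two exclusions, all from Table 1.

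**Step 1: set the criteria side by side.** Assume that each person meets every other criterion.

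| Person | Table read literally | Table read with an unwritten exception for minor depressive disorder |
|---|---|---|
| Minor depressive disorder now; PHQ-2 and GAD-2 both below 3 | Excluded | Eligible |
| Minor depressive disorder now; PHQ-2 or GAD-2 at 3 or more | Excluded | Eligible |
| PHQ-2 or GAD-2 at 3 or more; no Axis I disorder in the past 12 months or in the history | Eligible | Eligible |
| PHQ-2 or GAD-2 at 3 or more; minor depressive disorder only in the past, more than 12 months ago | Excluded by the history criterion | Eligible |

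On the literal reading the first route is empty, and the second and third are narrowed but open.

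**Step 2: look for text that resolves it.** The inclusion criterion on major depression and anxiety disorders covers a narrower set of conditions and does not mention minor depressive disorder. It therefore neither creates nor cures the conflict. The history exclusion does carry an explicit exception, but only for non-psychotic unipolar major depression and anxiety disorder. Taken literally, a past major depression is allowed and a past minor depression is not. The Screening section adds nothing on the point.

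**Step 3: see how it reaches the refusal criterion.** Suppose, for illustration, that every eligible person is either randomised or refuses, and that R people refuse while 60 are randomised. The criterion is R / (60 + R) ≤ 0.20, so R ≤ 0.25 × 60 = 15, with 60 + 15 = 75 eligible.

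- With 16 refusals, 16 / 76 = 21.1 % and the criterion fails. If one of the 16 has minor depressive disorder and is reclassified as ineligible, 15 / 75 = 20.0 % and it is met.
- With 15 refusals the criterion is met. If instead one of the 60 randomised has the diagnosis and is reclassified as ineligible, 15 / 74 = 20.3 % and it fails.

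The reading can move the result in either direction. At the margin, one person is enough. These counts are not a forecast, because the article does not say how many screened people would carry the diagnosis.

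**The case against.** The strongest reply is that the intent is obvious. The abstract, the aims, the Participants text and the description of the intervention all name minor or subthreshold conditions. A specific inclusion that names the index condition is ordinarily read as an exception to a general exclusion beside it. Staff may well be screening that way already, and the fuller protocol behind this article may contain the exception. This stands as a reason to rate the point lower, but it does not remove the contradiction. The neighbouring history exclusion shows that the authors wrote an exception where they wanted one. The problem is also two stated criteria in conflict, not detail left out of a condensed article.

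Three stronger readings are tempting and are not supported:

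- A reader might infer that a large part of the eligible pool is lost. The article gives no share, and it says that the intervention focuses primarily on people with subthreshold symptoms, who can enter by the PHQ-2 or GAD-2 without an Axis I diagnosis.
- A reader might infer that the pilot's findings on disorder incidence are compromised. The abstract lists recruitment, adherence, retention and acceptability as primary outcomes. Study measures assigns the preemption of disorders, as a primary outcome, to the full-scale trial, and the pilot is stated not to be powered to test a hypothesis.
- A reader might count the history criterion as a second, independent defect. It bites on minor depressive disorder only under the same literal reading, and it can be read as meaning disorders apart from the index condition. It is a secondary part of one conflict.

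It is also fair to say that the refusal proportion can be calculated under either reading. What is unclear is which population it describes.

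**Conclusion.** The contradiction is real and can be seen from Table 1 alone, since the table supplies the Axis I label. Taken as written, one of the three entry routes is closed, and people who qualify by a screening score are also removed if they have the diagnosis. Alternatively, if screeners assume an exception, each such enrolment departs from the written criteria.

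The number of people affected is unknown. The conclusion rests on the exclusion being applied as worded. If it has been applied uniformly with the exception understood, the harm is limited to the wording. A moderate internal inconsistency is the right rating. It deserves correction because a definitive trial could inherit the criteria and because eligibility feeds a stated success criterion. It does not make the pilot unworkable, so it is not a must-fix item.

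**What to change.** Reconcile the two criteria in line with the stated aims by adding *other than minor depressive disorder* to the 12-month Axis I exclusion. Word the psychiatric-history exclusion consistently, so that minor depressive disorder is treated the same way in both. If the sponsor really means to exclude these people, the first inclusion route and the references to minor depression in the population description should be removed instead.

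Trial status says that recruitment and intervention delivery are under way. The sponsor should therefore also check how people already screened were classified, record which reading was used, and use that reading when reporting the number eligible and the refusal proportion.

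The text change is one phrase in each of two criteria. Because the protocol is approved by the institution's review board and the study is running, the cost also includes a clarification or amendment there and a review of the screening log. Sample size, randomisation and outcome measures do not change.

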### Recruitment

A community-based recruitment strategy employing locations that older Latinos are likely to frequent (such as churches, laundromats, libraries, and hair salons) will be used. It is the mission of the Community Engagement Group to help facilitate links between researchers at UM and the community. The recruitment efforts will be led by the CHW, who will work with the community advisory board and the study team to devise recruitment strategies that are most appropriate. To the extent possible these would be informed by already successful attempts in this community. Examples include targeting high-volume areas (such as laundromats, hair salons, and flea markets) and using ads in the local Latino press (such as the newspaper and radio). In addition, local housing authorities, senior centers, and community health centers will be informed of the study and provided with promotional materials. The Miami-Dade County Parks and Recreation Department puts on regularly scheduled health fairs in which residents are provided with free health screens. The principal investigator (PI) and CHWs will be present at these events to ensure that every older adult who comes in for a health screening will be screened for depression and anxiety. At the same time, the UM Public Relations (PR) department will be informed and notified of the ongoing research. The PR department will be provided with the promotional materials for the study. UM sites such as those that make regular postings and newsletters will also be contacted and provided with an approved ad or communication regarding the project. The ad will also be posted in non-UM newsletters and advertisement sections.

### The interventions

The HOLA intervention focuses primarily on indicated prevention, enrolling participants with subthreshold symptoms. The conceptual model, which forms the basis of the intervention (Fig. 1), is designed to address depression and anxiety symptoms as well as physical and psychosocial functioning. It will achieve this goal through two related mechanisms, Behavioral Activation (BA) and Social Learning Theory (SLT) [28, 40]. The intervention uses a BA [28] approach to engage in a physical activity routine as well as a pleasant events schedule to preempt incident and recurrent episodes of major depression and anxiety disorders and to reduce symptom severity. To complement this process, the constructs of observational learning, reinforcement, and enhanced self-efficacy postulated in SLT [40] are used. The relationship between the participants and the CHW capitalizes on the personal relationship to motivate, model, and maintain health behavior change. The CHW holds the individuals accountable and individuals hold themselves accountable to the group, providing extra motivation to engage in the intervention.

